4.3.3 Tertiary effect parameters are

- The extent of exercise in follow-up periods I and II, measured as a combined assessment of the exercise effort by the Borg scale and an external evaluation.
- Cortisol concentration at inclusion (in saliva or diurnal urine) compared with cortisol after 2, 9 and 29 weeks.
- The cortisol concentration in diurnal urine at inclusion is compared with the cortisol concentration in saliva at inclusion.
- The percentage of variability of depression severity at week 0 (calculated from the Preskorn scores during the first 6 days of the study) is compared to change in depression severity after the 3 sleep deprivations at week 2.
- In treatment group B, the idiographic effect parameter is the percentage change from inclusion to week 29.

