**3. OBJECTIVE**

The main objective of the trials is to examine whether sleep deprivation in combination with light treatment, duloxetine and maintenance of diurnal rhythm (Group A) is able to induce a faster onset of action and lasting antidepressive response compared to an individually designed exercise programme in combination with treatment with duloxetine (Group B).

Secondary objectives are studies of cortisol concentration, variability of the degree of depression, the idiographic method and finally, applicability and effect of exercise over 9 weeks under supervision. The following hypotheses ar going to be tested in the study:

- Is sleep deprivation in combination with duloxetine, light and maintenance of diurnal rhythm (Group A) able to induce a greater degree of response or remission than exercise in combination with duloxetine (Group B). The hypothesis is tested after 2, 9 and 29 weeks of therapy?
- Is it possible for patients with major depression during the supervised course of treatment of 9 weeks to achieve the National Health Board's recommendation of exercising 30 minutes per day, and is there any association between the exercise effort and the degree of depression after 29 weeks?
- Is the cortisol concentration as measured in urine and saliva the beginning of week 2 correlated to the severity of depression as measured after 2, 9 and 29 weeks of therapy?
- Is the concentration of cortisol measured in saliva correlated with the concentration of cortisol in diurnal urine?
- Is the idiographic method more sensitive to change of degree of depression than clinician- and patient-rated scales and questionnaires for depression?
- Can variability in the degree of depression as measured with the Preskorn scale (see psychometrics) predict response to sleep deprivation?

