- At each visit, the patients are taught how to maintain their diurnal rhythm after discharge by an approximate bed time at 11 p.m. and a getting-up time at 8 a.m. the very latest. The patients receive instructions about the use of the medication and sleep diaries.
- Apart from exercise, the patients are allowed to join all milieu-therapeutic activities in the ward.

Group B

- In one of the first few days after admission, Group B patients are instructed by a physiotherapist in an individually designed exercise programme. A plan for follow-up meetings with the physiotherapist is agreed upon. The number of follow-up meetings is the same as the number of visits to the study clinicians who assess treatment effect, and if possible all planned visits during the study will be scheduled together. The patients are allowed to join all milieu-therapeutic activities in the ward.
- Duloxetine treatment continues unchanged, with a dose of 60 mg daily.
- During the first 24 hours in the hospital the patients collect 24-hour urine for the measurement of cortisol. On their second day the patients give saliva samples in the morning for the measurement of cortisol.

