**4.7. Biochemical and physical tests**

Blood samples are taken at inclusion to be analysed for TSH (thyreoidea stimulating hormone), haemoglobin, creatinine, alanine transferase, alkaline phosphatase, ionised calcium, folic acid, cobalamin and urine hCG (in women). An ECG is made. Group B patients are asked to collect diurnal urine to be examined for cortisol on the first day of hospitalisation and again after 9 weeks, at the end of the study. On the second day of hospitalisation, group B patients give saliva samples, also for cortisol analysis. This provides an opportunity for comparing cortisol in diurnal urine and saliva. The saliva samples are taken in the morning, 15, 30 and 60 minutes after awakening.

Blood pressure is measured at inclusion and after 9 weeks by automatic blood pressure monitor while the study subject is seated. The measurement is repeated several times, until the blood pressure is reproducible. The value from the arm giving the highest result will be used. ECG is made at inclusion and is assessed by a doctor with medical expertise.

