**11. STATISTICS**

To analyse the number of patients with response or remission at three defined points in time (weeks 2, 9 and 29), Chi2 distribution is used. To do this, the Last Observation Carried Forward (LOCF) is employed. The assessment of the longitudinal courses of response and remission (and sustained response and remission) uses survival analysis (Kaplan-Meier survival-analysis) including log-rank test to calculate p values (Stassen et al 1993). Furthermore, the Mixed Model Repeated Measures (MMRM) (Brown et al. 1999) will analyse readily available depression scores to determine the difference between the two groups. Thus, MMRM does not use LOCF. The association between cortisol and depression scores and the association between urine and saliva cortisol has been calculated by means of the Spearman correlation coefficient *rho*. The same statistical method will be used to test the association between the various degrees of depression and the effect of sleep deprivation. The idiographic method will be analysed by means of MMRM. Exercise will be analysed as the percentage of compliance to the predefined goal (30 minutes exercise daily). Moreover, the achieved amount of exercise (combined score of the Borg scale and the amount of performed exercise) will be graded into light/moderate/intensive in follow-up phase I. It will be compared with the degree of response and remission in week 29 and analysed by Chi2 distribution. The number of study subjects has been calculated on the basis of an expected depression score of 24 on the 17-item Hamilton Depression Scale at inclusion into the study for both groups. After 9 weeks of treatment a decrease to 10 in group A and to 13 in group B is expected. The expected standard deviation is 4. With a type-I error of 0.05 and 0.90 power, 39 patients are required for each group.

No interim analyses have been planned.

GCP guidelines permit that patients may be excluded from the data analysis after the end of the study, if eligibility violations have taken place and if this was not known during the project. This may refer patients who have fulfilled the inclusion criteria, but have not taken any of the study medication, or have taken other prescriptions without telling the investigator, and where these violations were not known until the end of the study. All other patients assessed at the time of inclusion in the study are included in the statistical analyses according to the intention-to-treat method.

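### Urine cortisol is defined as the concentration in a full 24-hour collection, so urine volume enters the analyses that use urine; the saliva-severity correlations are not affected

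*Protocol*

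**What the plan says.** **The sample.** Section 4.1.4 (Group B) asks for a whole-day collection: "During the first 24 hours in the hospital the patients collect 24-hour urine for the measurement of cortisol". Section 4.7 repeats this: "Group B patients are asked to collect diurnal urine to be examined for cortisol on the first day of hospitalisation". Flowchart 2 schedules further urine collections at weeks 9 and 29. Saliva appears only in week 1, in Flowchart 1.

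**The measure.** Section 3 states two cortisol hypotheses, both in terms of concentration: "Is the cortisol concentration as measured in urine and saliva the beginning of week 2 correlated to the severity of depression", with severity taken at weeks 2, 9 and 29, and "Is the concentration of cortisol measured in saliva correlated with the concentration of cortisol in diurnal urine". Section 4.3.3 uses the same term in two tertiary parameters: "The cortisol concentration in diurnal urine at inclusion is compared with the cortisol concentration in saliva at inclusion" and "Cortisol concentration at inclusion (in saliva or diurnal urine) compared with cortisol after 2, 9 and 29 weeks".

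**The analysis.** Section 11 reads: "The association between cortisol and depression scores and the association between urine and saliva cortisol has been calculated by means of the Spearman correlation coefficient". It mentions no adjustment for volume.

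**What does not appear.** The supplied text mentions neither urine volume, nor amount per 24 hours, nor a correction for urine creatinine. Creatinine occurs once, in the section 4.7 list of samples taken at inclusion ("haemoglobin, creatinine, alanine transferase, alkaline phosphatase, ionised calcium, folic acid, cobalamin and urine hCG (in women"), and not as a correction applied to the 24-hour urine.

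**The concern.** A 24-hour collection allows the total daily output to be computed. If only the concentration is analysed, that information is lost and the value depends on how much urine the patient passed. Two patients with the same cortisol output who pass 1 litre and 2 litres differ two-fold in concentration. Spearman's coefficient does not remove this, because it ranks the already diluted values.

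Two things are at stake. The correlations that use urine would tend to be weaker than the same correlations computed on excretion, in a sample of about 50 patients. And where urine cortisol is compared between visits, a change in fluid intake would look like a change in cortisol. Because saliva is scheduled only in week 1, any later comparison with repeat cortisol has to rest on urine.

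**Working it through.** **The protocol's own figure.** The only sample-size calculation is in section 11 and concerns HAM-D17: difference 13 − 10 = 3, SD 4, type I error 0.05 (taken as two-sided), power 0.90. The normal formula gives 2 × (1.96 + 1.28)² × 4²/3² = 37.4, so 38 per group; the t-based version gives 38.35, so 39. The stated 39 reproduces, but it says nothing about cortisol. No figure is stated for any cortisol analysis.

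**Which correlations are exposed.** Section 3 implies seven:

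- urine with severity at weeks 2, 9 and 29: three, exposed to volume;
- urine with saliva: one, exposed to volume;
- saliva with severity at weeks 2, 9 and 29: three, not exposed.

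So four of the seven are exposed.

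**Size of the effect.** On the log scale, log concentration = log excretion − log volume. Let k = SD(log volume)/SD(log excretion). If volume is unrelated to excretion, to severity and to saliva cortisol, then

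r(concentration) = r(excretion) / sqrt(1 + k²).

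Inputs:

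- n = 50: planned Group B size, section 12. n = 39 is shown as well, being the per-group requirement in section 11.
- k: not in the documents; assumed 0.25 to 1.0.
- True correlation with excretion: not in the documents; assumed 0.40, with 0.30 and 0.50 as alternatives.

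Power uses Fisher's z at two-sided 0.05 with variance 1.06/(n − 3), after converting the correlation to the Spearman scale by (6/π) × arcsin(r/2). For r = 0.40 that gives 0.385. Then arctanh(0.385) = 0.405, multiplied by sqrt(47/1.06) = 6.66 this is 2.70, and 2.70 − 1.96 = 0.74, so power is 0.77.

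| k (assumed) | Factor | 0.40 becomes | Power, n = 50 | Power, n = 39 |
|---|---|---|---|---|
| 0 (excretion used) | 1.00 | 0.40 | 0.77 | 0.66 |
| 0.25 | 0.97 | 0.39 | 0.74 | 0.63 |
| 0.50 | 0.89 | 0.36 | 0.66 | 0.55 |
| 0.75 | 0.80 | 0.32 | 0.56 | 0.46 |
| 1.00 | 0.71 | 0.28 | 0.46 | 0.37 |

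Over the same range of k at n = 50, power for a true 0.30 goes from 0.50 to between 0.48 and 0.28, and for a true 0.50 from 0.94 to between 0.92 and 0.65.

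**If volume and output are related.** With a correlation c between log volume and log excretion, and the other variable linked to volume only through excretion, the factor is (1 − ck)/sqrt(1 + k² − 2ck). At k = 1 it is 0.81 for c = −0.3, 0.71 for c = 0 and 0.59 for c = 0.3. At k = 0.25 it stays between 0.97 and 0.98 for all three.

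**The case against.** **Concentration may be loose wording.** Where the protocol describes procedures (sections 4.1.4 and 4.7) and the analysis (section 11), it speaks simply of cortisol. In section 4.3.3 one parameter starts with concentration and ends with plain cortisol. The term also covers saliva, where it is the natural one, and a whole-day collection suggests that daily output was intended. This lowers certainty. It does not remove the point, because the hypotheses and parameters consistently name concentration and nothing corrects them.

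**Volume may already be recorded.** The table of contents lists an enclosure with instructions for the 24-hour collection, and section 6 places cortisol results in the patient record. Neither is in the supplied text. A reader might infer that volume is not measured; the documents do not show that. What can be criticised is the stated definition of the measure.

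**Not every cortisol correlation is affected.** A reader might infer that all the cortisol analyses are weakened. Urine volume cannot alter saliva cortisol, so three of the seven correlations stand as planned, and they offer a second route to the cortisol-severity question.

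**The size is assumed.** Neither k nor the true correlation comes from the protocol. At k = 0.25 the loss is close to nothing. This objection stands in full.

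**Excretion has its own error.** A missed void lowers the computed excretion, while concentration is less sensitive to lost volume. Incomplete collection is plausible during the first 24 hours on a ward. This also stands and belongs in the fix.

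**Conclusion.** As written, sections 3 and 4.3.3 put urine volume into the four correlations that use urine and into any comparison of urine cortisol over time. The expected shrinkage is a factor of 0.97 to 0.71 for an assumed k of 0.25 to 1.0. For an assumed true correlation of 0.40 in 50 patients, power falls from 0.77 to between 0.74 and 0.46.

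This is attenuation in expectation and rests on volume being unrelated to output, severity and saliva cortisol. If volume were itself related to severity or to saliva cortisol, the direction of the distortion would no longer be fixed.

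A reader might conclude that a real cortisol association is likely to be missed. The documents do not support that: they give no k, and the loss may be negligible. Nor do the primary or secondary efficacy results depend on these analyses, which are tertiary, confined to Group B and have no sample-size basis. The point is a cheap improvement of low priority.

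**What to change.** - In sections 3 and 4.3.3, define urine cortisol as 24-hour excretion: concentration multiplied by the total collected volume. Use that value in the urine-saliva correlation, the three urine-severity correlations and any comparison of urine cortisol between visits. Leave the saliva measure as it is.
- Make sure that the total volume is recorded with each collection. If the collection instructions already require it, a cross-reference is enough.
- Record whether each collection was complete, and state beforehand that incomplete ones are flagged or excluded, because they understate excretion. Keep concentration as a sensitivity analysis.

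The cost is a change of wording and, at most, two extra entries per collection. No visit, sample or patient is added. If volume is not recorded at the time, excretion cannot be recovered later, so this should be settled before collections begin.

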4.1.4. Hospitalisation phase: week 1 (7 days)

All study participants are hospitalised and meetings with the study investigators are envisaged for each working day. All patients (both groups, A and B) are hospitalised in an open in-patient ward. See Figures 1 and 2. Previously hospitalised patients can be discharged if their condition permits it. Patients admitted due to study participation will be discharged 6 days after admission unless their condition does not allow it. If the patient stays in hospital the trial will follow the usual guidelines, but the visits will take place in the in-patient ward whenever necessary.

Group A

- During hospitalisation, Group A patients go through 3 sleep deprivations, the first one on the day of admission (see Figure 2). Sleep deprivation is mainly carried out as total sleep deprivation, i.e. the patients stay awake all night. However, in some cases partial sleep deprivation may be used, in which the patient is woken up at 02.00 a.m. and has to stay awake for the remains of the night. This can be done either due to an individual patient evaluation made by the investigator or due to a wish on the part of the patient. There may be good reason for using partial sleep deprivation in case of medical diseases such as diabetes, where the blood sugar level can get out of balance, or in other diseases that may be influenced by a longer wake period. Also elderly patients expect not to be able to stay awake all night may also profit from partial sleep deprivation. Patients who experience that their first and total sleep deprivation is too demanding may also switch over to partial sleep deprivation. A combination of total and partial sleep deprivation is thus permitted.
- In the evening after each sleep deprivation the patients must go to bed at 9 p.m. at the very latest and get up at 7 a.m. the following morning (sleep-phase advance).
- The treatment with duloxetine continues unchanged, with a dose of 60 mg daily.
- The patients are informed about light treatment on the day of admission which is given for the first time the following morning and subsequently each day of the study period. The duration of light treatment is 30 minutes. The time of day of the light treatment is decided after completion of the MEQ questionnaire (see psychometrics paragraph). In addition to this, to fight tiredness, the patients take light treatment at 4 a.m. each night during the period of sleep deprivation.

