| **Study period and duration** | **Medication start phase:**  **7 days** | **Hospitalisation:**  **7 days**  Visits on week days | **Follow-up phase I:**  **7 weeks**  **Visits each week** | | | | | | | |
| --- | --- | --- | --- | --- | --- | --- | --- | --- | --- | --- |
| **Week no.** | **0** | **1** | **2** | **3** | **4** | **5** | **6** | **7** | **8** | **9** |
| **Visit no.** | **1 (Inclusion)** | **2** | **3** | **4** | **5** | **6** | **7** | **8** | **9** | **10** |
| **M.I.N.I.+ SCID I and II**  **SPAQ + MEQ + DIAD + SPS** | x |  |  |  |  |  |  |  |  |  |
| **Hamilton + MES + MAS + MDI + UKU + WHO-5** | x | x | x | x | x | x | x | x | x | x |
| **Preskorn** | daily | daily | daily | daily | daily | daily | daily | daily | daily | daily |
| **Borg scale + external assessment (exercise)** |  | x | x | x | x | x | x | x | x | x |
| **SCL-92** | x | x | x | x | x | x | x | x | x | x |
| **Idiographic method (gr. B)** | x | x | x | x | x | x | x | x | x | x |
| **EKG + Blood pressure + Blood samples** | x |  |  |  |  |  |  |  |  | x |
| **Collecting diurnal urine (gr. B)** |  | x |  |  |  |  |  |  |  |  |
| **Saliva samples (gr. B)** |  | x |  |  |  |  |  |  |  |  |
| **Sleep, light, medication and exercise diaries and status** | x | x | x | x | x | x | x | x | x | x |
| **Stanford Sleepiness Scale** |  | x |  |  |  |  |  |  |  |  |
| **Expectation to treatment** | x |  |  |  |  |  |  |  |  |  |
| **Evaluation of treatment** |  |  | x |  |  |  |  |  |  | x |
| **TEMPS-A** |  |  |  |  |  |  |  |  |  |  |

**Flowchart 1(week 0 to 9, duration 9 weeks**)

| **Study period and duration** | **Follow-up phase II:**  **20 weeks**  **Visit every 4th week** | | | | | |
| --- | --- | --- | --- | --- | --- | --- |
| **Week no.** | **9*** | **13** | **17** | **21** | **25** | **29** |
| **Visit no.** | **10** | **11** | **12** | **13** | **14** | **15** |
| **M.I.N.I.+ SCID I and II**  **SPAQ + MEQ + DIAD + SPS** |  |  |  |  |  |  |
| **Hamilton + MES + MAS + MDI + UKU + WHO-5** | x | x | x | x | x | x |
| **Preskorn** | weekly | weekly | weekly | weekly | weekly | weekly |
| **Borg scale + external assessment (exercise)** | x | x | x | x | x | x |
| **SCL-92** | x | x | x | x | x | x |
| **Idiographic method (gr. B)** | x |  |  |  |  | x |
| **EKG + Blood pressure + Blood samples** | x |  |  |  |  | x |
| **Collecting diurnal urine (gr. B)** | x |  |  |  |  | x |
| **Saliva samples (gr. B)** |  |  |  |  |  |  |

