The self-rating scales used are the SCL-92 (Symptom Checklist) (Olsen et al 2004) and the Major Depression Inventory (MDI) (Bech et al. 2001, Olsen et al. 2003), - the MDI, however, in a modified version in which severity as well as frequency of the depression symptoms are assessed .

To subjectively assess the day-to-day and time of day variability of the degree of depression, the Preskorn scale will be used daily at 9 and 12 a.m. and 3, 6 and 9 p.m., and at awakening and bedtime during the first week prior to hospitalisation. It will be examined whether variability of degree of depression and diurnal variation are predictors of response to sleep deprivation. During the first 9 weeks of the study, the Preskorn questionnaire will also be used for daily measurements of degree of depression, and subsequently once weekly until week 29.

A questionnaire has been developed for the patient's assessment of his/her expectation to treatment, and thus an evaluation of an even distribution of the placebo effect among the two treatment groups. It is filled in at inclusion, after the patient has received detailed information about the project.

The WHO-Five Well-being Index (WHO-5) will be used at each visit to assess quality of life. This instrument contains 5 questions and has been validated in a number of studies (Bech 2004).

Specific questionnaires have been developed to capture the patient's impression of the treatment after 2 weeks (i.e. immediately after discharge), also offering the possibility of open statements. After 9 and 29 weeks, the patients are asked for repeated assessments of their treatment.

The patient's temperament is assessed by the TEMPS-A at the end of the study, in week 29 (Akiskal et al. 2002). This questionnaire contains five scales examining personality traits that have been present throughout the patients' lives (character traits). The five traits are: depressiveness ("depressive"), anxiousness ("anxiety"), irritability ("irritable"), mood swings ("cyclothymia") and extraversion, energeticness ("hyperthymia"). The reason for using this scale at the end of the study is that the depressive condition, which expectedly is less marked at the end of the study, at an earlier stage would affect the self-assessment of the person and thus rather reflect the current condition than character traits.

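### Whether week-0 Preskorn variability predicts response to sleep deprivation is examined in Group A alone, so this tertiary analysis cannot separate treatment-specific prediction from general prognosis

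*Protocol*

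**What the plan says.** Protocol section 3 (Objective) lists the question as the last of its hypotheses: "Can variability in the degree of depression as measured with the Preskorn scale (see psychometrics) predict response to sleep deprivation". Section 4.2 (Psychometrics) repeats it and adds time-of-day variation: "It will be examined whether variability of degree of depression and diurnal variation are predictors of response to sleep deprivation".

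Section 4.3.3 makes it a tertiary parameter. The marker is "The percentage of variability of depression severity at week 0 (calculated from the Preskorn scores during the first 6 days of the study"), and it "is compared to change in depression severity after the 3 sleep deprivations at week 2". Section 4.1.4 gives the intervention to one arm only: "During hospitalisation, Group A patients go through 3 sleep deprivations, the first one on the day of admission".

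Section 11 (Statistics) says of the cortisol associations that each "has been calculated by means of the Spearman correlation coefficient" rho. It continues: "The same statistical method will be used to test the association between the various degrees of depression and the effect of sleep deprivation". No other test in section 11 fits the Preskorn question.

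No section plans the same correlation in Group B, a comparison of two correlations, or a variability-by-group interaction. Flowchart 1 nevertheless schedules the marker for everyone. Its row reads "Preskorn | daily | daily | daily" with no group restriction, and the Hamilton row is likewise unrestricted, whereas the idiographic, urine and saliva rows are marked for Group B.

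**The concern.** The question names a treatment, but the analysis has no comparator. A correlation within Group A between variability and improvement can arise in two ways: variable patients gain more from the Group A treatment, or variable patients improve more whatever they receive. A one-arm coefficient is the same in both cases.

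The second explanation is open on the protocol's own design. Both groups start duloxetine in week 0 (section 4.1.3) and both are hospitalised in week 1 (section 4.1.4), so week-2 change in Group A is not change from sleep deprivation alone. The marker is also collected while patients are already on duloxetine, in both groups.

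What is at stake is the interpretation of an exploratory result. A general prognostic marker could be read as a way of choosing patients for sleep deprivation. The randomised comparison that would help tell the two apart is already being collected.

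**Working it through.** **The protocol's own figure.** The only sample-size calculation (section 11) concerns HAM-D17 at week 9: means of 10 and 13, SD 4, type-I error 0.05, power 0.90. The two-sided normal formula gives 2 × (1.960 + 1.282)² × 4² / 3² = 37.4, so 38 per group. The t-test version gives 38.35, so 39, as stated. It does not concern the predictor aim, for which no figure is given. Section 12 plans 50 per group, which is used below.

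**Assumption.** The documents give no correlation between variability and improvement. The values 0.2 to 0.5 are assumed, with bivariate normal data and two-sided 5% tests.

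**Tests compared**
- One-arm test: Spearman in Group A alone. On the Fisher-z scale the SE is √(1.06/(n − 3)) = √(1.06/47) = 0.150.
- Contrast: difference of the two Fisher-z values, A minus B, with SE √(2 × 1.06/47) = 0.212.

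**Purely prognostic marker (same correlation r in both groups), 10,000 simulated trials each, 50 per group**

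| r | One-arm test significant | A-versus-B contrast significant |
|---|---|---|
| 0 | 5% | 4% |
| 0.2 | 26% | 5% |
| 0.3 | 52% | 4% |
| 0.4 | 79% | 5% |
| 0.5 | 95% | 5% |

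With 39 per group, the one-arm figures for r = 0.2, 0.3 and 0.4 are 21%, 42% and 68%, and the contrast stays near 5%.

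*Check by formula.* The Spearman value is (6/π) × arcsin(r/2), which gives 0.191, 0.288 and 0.385 for r = 0.2, 0.3 and 0.4. The Fisher-z values are 0.194, 0.296 and 0.405. Dividing by 0.150 and subtracting 1.96 gives about −0.67, 0.01 and 0.74, hence about 25%, 50% and 77%. This agrees with the simulation. The one-arm column is therefore just the power of a Spearman test at n = 50. The point is that this power is spent on a non-specific association.

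**Marker truly specific to Group A (correlation 0 in B), power of the contrast at 50 per group**

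| r in A | 0.3 | 0.4 | 0.5 | 0.6 |
|---|---|---|---|---|
| Power | 28% | 48% | 70% | 88% |

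For 80% power the Fisher-z difference must be about 2.8 × 0.212 = 0.59, a rank correlation of about 0.53 in A against 0 in B.

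**Regression to the mean.** Section 4.2 says a single score may be unreliable in highly variable patients, and entry requires HAM-D17 of at least 13. Assume a within-patient SD averaging 3 (varying by 1 across patients), a between-patient SD of 3 to 4, and no true link between variability and improvement. At a mean inclusion score of 24, the value section 11 expects, the resulting correlation is only about 0.01. At a mean of 17 it is about 0.09. Other runs under similar assumptions gave up to 0.04 and 0.13. A rank correlation of 0.04 makes the one-arm test significant in about 6% of trials, and 0.13 in about 14%.

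**The case against.** **The question can be read within one arm.** It may simply ask which of the patients given sleep deprivation improve, and a Group A correlation answers that. This stands. It is why rewording the result as an association within Group A is an acceptable alternative. It does not license a claim that the marker is specific to sleep deprivation.

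**The Spearman link is an inference.** Section 11 refers to degrees of depression, not variability or the Preskorn scale. A reader might infer that the protocol plainly fixes a Spearman test of variability, but the text does not say so. The one-arm structure does not depend on that reading, because section 4.3.3 itself ties the outcome to the sleep deprivations.

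**The percentages rest on assumed correlations.** This stands. A reader might infer that the trial will report a false predictor. The documents do not show that variability is prognostic, and if it is not, the one-arm error rate is the nominal 5%.

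**Regression to the mean.** A reader might expect it to drive a spurious result. At the expected inclusion score of 24 it adds almost nothing. Section 4.3.3 also fixes neither the scale nor the starting point of the change, so the inclusion score may not be the baseline at all.

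**The contrast is not a pure test of sleep deprivation.** Group A also receives light and sleep-phase advance, and Group B receives exercise, which section 4.1.7 calls another chronotherapeutic intervention. This limits what an interaction means. However, the same section says Group B functions as a control in follow-up phase I, so the comparison remains informative.

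**Detail for a tertiary aim is often left to a statistical analysis plan.** That is fair for the model's specification. But the protocol itself fixes the marker and an outcome that only one arm can have.

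**Conclusion.** The point holds in a limited form. As written, the analysis cannot distinguish prediction specific to the Group A treatment from general prognosis, although the Group B data that would help are scheduled. For a purely prognostic marker with an assumed correlation of 0.2 to 0.4, the one-arm test would be significant in about 26% to 79% of trials at 50 patients, against about 5% for the contrast. The size depends entirely on that assumption.

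A reader might infer that the trial's main conclusions are at risk. They are not: this is a tertiary, exploratory aim, and no primary or secondary efficacy parameter or sample-size figure depends on it. It is a cheap improvement to the analysis and wording, not a defect of the design.

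**What to change.** Keep the Group A Spearman coefficient, compute the same coefficient in Group B over the same interval, and show both. Add one exploratory model in both groups: week-2 HAM-D17 on group, week-0 Preskorn variability, their interaction and inclusion HAM-D17. Report the interaction with its 95% CI.

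State that the interaction contrasts the package of sleep deprivation, light and sleep-phase advance with exercise, on a common background of duloxetine and hospital care. Claim a predictor specific to the Group A treatment only if the interaction supports it. Otherwise describe the result as an association with improvement within Group A. In section 11, name the marker explicitly in place of the reference to degrees of depression.

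The cost is analysis work and a few sentences, with no new data. The downside is low precision, as the power figures above show, so the likely outcome is a wide interval and a more cautious claim. For that reason the interaction should be reported as an estimate and not treated as a decisive test.
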